
### Ethics

This is a questionnaire for professionals who will be verbally informed as to the objectives and content of the questionnaire prior to being interviewed in their work centres. Participation is voluntary. Data analysis will remain totally anonymous to make identification of the participating professionals through their answers impossible. Neither will professionals who decide not to participate be identifiable. No direct intervention will be made (pharmacologic, educative, formative or preventive) in patients or healthcare users or in professionals except for knowing their opinions. The questionnaires for the families will be hetero-administered through a cultural mediator and will not include any information which will allow identification of the person interviewed. The questionnaire will be given in a specific room of the centre to ensure confidentiality and privacy for the participants. Data analysis will remain totally anonymous to make identification of the participating migrant people through their answers impossible. All the databases generated will retain adequate anonymity. Informed consent will be requested from participants in the study. In the case of migrant people, cultural mediators may be required to obtain this informed consent. The management personnel of the centres will be informed of the undertaking of the study and the study has been approved by the ethical committee of the Clinical Research Ethics Committee of the Primary Care Research Institute IDIAP-Jordi Gol (Barcelona, Spain).

## Discussion

The arrival to Spain of families from countries of sub-Saharan Africa in the decade of the 80's, has allowed different cultural realities to be discovered and has shown the presence of traditional practices which are harmful to the health of the girls, daughters of migration, mainly born in Spanish territory but without Spanish nationality. In the case of Spain there is an ethnic reality (mainly from Western Africa), a geographical distribution (basically Catalonia and Aragon) and an accessible number of population which should allow privileged sensitisation [25] since these are communities which are well settled in Spain with strong community links, universalised healthcare and accessability from primary care in all the municipalities of residence.

On the other hand, the growing demographic weight of these communities will no longer make the presence of girls at risk of undergoing FGM exceptional in the near future [30].

We are searching for answers related to whether, when faced with an FGM issue, primary healthcare professionals: a) know and correctly identify the typology of the FGM and its implication for the health of the women, b) know the legal framework and its consequences in Spain, c) have ethical and interventional dilemmas when faced with a hypothetical case of FGM, and d) consider themselves capable of intervening.

Knowledge of the attitudes and needs for trainning of the healthcare professionals of our country, regarding the practice of an emerging health problem such as FGM, should favour the development of strategies of sensitisation and detection of these situations. These strategies could therefore lead to the implementation of educational programmes to develop professional skills in the approach, detection and prevention of this type of situations from the healthcare system to avoid specific legislation related to problems associated with the health and equality of people and thereby make such laws the last step in the chain of prevention.

The approach to this problem raises ethical and legal dilemmas to the primary care professionals related to the consequences of both their intervention as well as non intervention in relation to a suspected case of FGM or the detection of risk for the girls [31-33].

A preventive interdisciplinary task which will allow the designing of strategies focused on the eradication of these practices and evaluation which allows knowledge of the cases produced and the resolution of conflicts considered in both Spain and Africa are therefore essential. Consciencious, reflexive and rigourous work of information, training and sensitisation are necessary. To do this, the proposal herein presented will provide better knowledge of the problem of FGM and how primary care professionals may approach this problem since there are no studies in Spain and very few in Europe. Training strategies and the development of guidelines may therefore be elaborated to enable primary care professionals to prevent and treat this new problem in the PHC.

On the other hand, it may be a model of positive intervention through transcultural care which is respectful of the values and beliefs of the people.

The main limitation of this study is the little collaboration received from the professionals at the time of performing the survey. To surpass this limitation, different researchers of the project will go to the primary healthcare centres to inform the professionals and increase their participation with distribution in a specific meeting with all the professionals of the PHC.

The presence of communities of sub-Saharan immigrants in our area is very concentrated in determined zones of each municipality thereby implying that the level of sensitisation for the problem of the study may vary greatly based on the demographic reality of each PHC. This concentration of immigrant communities in determined areas will not influence the results since our target population is all the professionals regardless of the zone in which they work. There is, therefore, no risk of a biased exploration of this knowledge, attitudes and practices based on the greater or lesser degree of exposure to the study subject. There will obviously be different levels of implication and sensitisation towards the subject which will be shown in the results of the study. With respect to the families, this geographical concentration will facilitate access to the communities although we are aware that there may be social or group conditioners which may influence in the perception of the problem on behalf of the interviewers and in their responses.

The approach to subjects such as FGM, which are closely linked to the identities and cultural backgrounds of the communities, is not easy and thus, we expect to encounter resistance to the determination of the position of the families of the girls at risk. This is a question which has seldom been used externally and is very sensitive to positions which are defensive and closed to the familial-ethnic group setting. Intercultural mediators will help in this task although this will not necessarily guarantee our access to exploring these opinions.

This is a health problem, which is perhaps not very prevalent at present, but which surpasses the purely healthcare framework and confers:

• The violation of the most basic human rights: the right to physical integrity, to health and equality.

• The need for a transcultural approach to these questions which is closely linked to the identity of the migrant persons.

• The moral commitment of the healthcare professionals to avoid these traditional practices which imply a discriminatory, violent, degrading and painful treatment towards women.

Knowledge of these practices and preventive approaches from a transcultural perspective may represent a positive intervention model in relation to integrative care to migrant populations, which is respectful of their values and culture while being effective in the elimination of the physical and psychological consequences.

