There are few studies in Spain related to FGM in primary care. A previous survey carried out by investigators of our team of healthcare professionals in the county of the Maresme (Barcelona) [14,15] reported that 56% of those surveyed did not correctly identify the typology of FGM, 17% were not interested in the subject and their answer to the question "What would you do in the case of FGM?" was: "ignored". Twenty-one percent of the personnel of the sexual and reproductive healthcare programme, 7% of the paediatricians and 5% of the general medicine professionals declared having detected or known of some case in both mothers and daughters. This study demonstrated the profound lack of knowledge of the healthcare professionals in relation to this subject, raising the need to sensitise and educate from the privileged setting of primary healthcare, where most of the cases or situations at risk are detected. In other European countries the situation is similar [16-18].

The important migratory waves of sub-Saharan populations to the European Union in the last years are shaping societies which are increasingly more complex and diverse. The way to deal with the health problems affecting these people represents a challenge for the healthcare systems [19] and for the professionals working within who must develop approaches to allow transcultural care [20-22].

Based on the production of mapping FGM in Spain, with data of the census and municipal registration, updated in 2005 we have estimated that 3,659 women living in Catalonia have undergone some type of FGM; and 2,189 girls are at risk of having some type of FGM performed in the next years, without taking into account the impact of the last processes of immigration regularisation.

The deep-rooted social and cultural nature of these practices conditions their perpetuation despite the development of important legal restrictive initiatives in some countries of origin and destination of the immigrants. However, when migrant women return to their societies of origin they are points of reference, credibility and recognition in such transcendent aspects as reproductive health and education [23]. These women bear new knowledge acquired in Europe which has been incorporated and put into practice during the migratory process. Thus, the exploration of the beliefs and perceptions of the sub-Saharan immigrants attending our healthcare centres in relation to FGM may be of interest.

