#### Selection of healthcare providers

The study includes all the professionals of the PHC teams, the Sexual and Reproductive Healthcare Programme and the Departments of Paediatrics and Gynaecology-Obstetrics of the hospital centres. It will also include the social workers linked to PHC. In the Catalonian Healthcare System, primary healthcare professionals work in teams who attend the healthcare needs of the population assigned in a determined territory. These teams are made up of family physicians, general medicine physicians, paediatricians, nurses and social workers. Support programs are available within the setting of sexual and reproductive health and these are mainly constituted by gynaecologists, nurses and midwives. All these healthcare providers will be asked to voluntarily and anonymously participate in filling out the questionnaire.

The target population will therefore be all the healthcare providers of the previously mentioned groups and teams who will be contacted through the heads of the teams and informative sessions in each of the centres and departments. A response rate of around 75% has been estimated, similar to that obtained by the same system in a previous study by our group in 2001 and 2004 [14,15].

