Sample size: According to the last municipal registry data available (11% of the immigrant population, 13.5% of which is of sub-Saharan origin), the population eligible in our study area is of 7,200 individuals. We assume that the prevalence of FGM in most of these countries is above 80% according to the reports of international organisations [6]. With an alpha risk of 0.05% for a precision of ± 0.06 percentual units and assuming 10% of non-responders, a sample of 191 subjects is required.

Non responders: a questionnaire will be elaborated for the immigrants selected who refuse to participate in the study. This questionnaire will collect only sociodemographic data, country of origin, etnia, years of residence in Spain and the reason for refusal to participate as well as the name of the person who proposed their participation in the study (interviewer, mediator or both). The aim of this questionnaire is to identify differences between the responder and non responder immigrant populations.

With respect to the healthcare professionals, the different rates of participation in the Primary Healthcare Centres will be taken into account in the analysis. Thus, if necessary, the principal results will be stratified according to the rate of participation.

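### Targeting all professionals does not rule out exposure-related bias when about a quarter are expected not to respond, and conditional stratification does not correct the overall percentages

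*Protocol article*

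**What the plan says.** The Discussion accepts that exposure differs between centres: "the level of sensitisation for the problem of the study may vary greatly based on the demographic reality of each PHC". It then says that the concentration of communities "will not influence the results since our target population is all the professionals regardless of the zone in which they work". From this it draws the following conclusion, which it ties to differing exposure: "There is, therefore, no risk of a biased exploration of this knowledge, attitudes and practices".

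Other parts of the article bear on this:

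- Selection of healthcare providers: participation is voluntary and anonymous, and "A response rate of around 75% has been estimated, similar to that obtained by the same system in a previous study".
- The sample-size text that closes the section on immigrant families: differing participation between centres is to be taken into account in the analysis, and "if necessary, the principal results will be stratified according to the rate of participation".
- Data collection: a code on each form identifies the team, so that a response rate per centre can be obtained.
- Ethics: professionals who decline cannot be identified.
- Discussion, the paragraph just before the statement at issue: poor collaboration by professionals is named as the main limitation.
- Sample-size text, Study variables and Analysis plan: a non-responder questionnaire and comparison are described for immigrants. None is described for professionals.

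**The concern.** Inviting everyone prevents the investigators from over-selecting high-exposure zones. It does not prevent the professionals from selecting themselves by answering or not. The people described are those who respond, and whether they resemble the rest depends on why the rest did not. If staff who see more affected families, or who care more about the subject, respond at a different rate, the percentages for knowledge, attitudes, intended actions and previous contact will differ from those in the full target population.

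All three main objectives concern professionals, and the training needs (objective 4) are to be read mainly from the knowledge results. A reader told that exposure cannot bias these results has no reason to look for the problem. The planned analysis also produces no overall figure that allows for unequal participation.

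**Working it through.** **Inputs from the article.** Expected response RR = 0.75 (Selection of healthcare providers). In the earlier survey 56% did not identify the typology correctly (Background), so 100 − 56 = 44% are taken as correct. The 75% is carried over from earlier studies and has no formula to reproduce.

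**1. Size of non-response bias.**

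Bias = (1 − RR) × (p_responders − p_non-responders) = 0.25 × gap.

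| Gap (points) | Bias (points) |
|---|---|
| 10 | 2.5 |
| 20 | 5.0 |
| 30 | 7.5 |
| 40 | 10.0 |

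The article gives no value for the gap, and no sign.

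**2. Range for one knowledge item.** Suppose 44% of responders answer correctly. The full-population value is 0.75 × 0.44 + 0.25 × p_non-responders.

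- Non-responders at 20% (assumed): 0.33 + 0.05 = 38%.
- Non-responders at 68% (assumed, the same 24-point gap the other way): 0.33 + 0.17 = 50%.
- Extreme limits, non-responders at 0% or 100%: 33% to 58%.

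**3. What adjustment by centre can and cannot do.** All values here are assumed. Take two equal groups of centres, with 60% (A) and 20% (B) of staff highly exposed. Correct knowledge is 60% in highly exposed staff and 30% in the others.

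True values:

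- A: 0.6 × 0.6 + 0.4 × 0.3 = 48%.
- B: 0.2 × 0.6 + 0.8 × 0.3 = 36%.
- Overall: 42%.

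*Case (a): response depends on individual exposure, 0.9 if high and 0.6 if not.*

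- A: response 0.54 + 0.24 = 0.78; estimate (0.324 + 0.072)/0.78 = 50.8%, bias +2.8 points.
- B: response 0.18 + 0.48 = 0.66; estimate (0.108 + 0.144)/0.66 = 38.2%, bias +2.2 points.
- Crude overall: (0.396 + 0.252)/(0.78 + 0.66) = 45.0%, bias +3.0 points, at 72% overall response.
- Re-weighted to equal groups: (50.8 + 38.2)/2 = 44.5%, bias +2.5 points.

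*Case (b): response differs only between groups, 0.9 in A and 0.6 in B (75% overall).*

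- Crude overall: (0.9 × 0.48 + 0.6 × 0.36)/1.5 = 43.2%, bias +1.2 points.
- Re-weighted: (48 + 36)/2 = 42.0%, bias 0.

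Listing A and B separately leaves the crude overall figure where it was. Re-weighting removes the between-centre part of the bias and only that part. The positive sign here comes from the assumed values.

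**The case against.** The strongest reply is that the sentence concerns geography. It follows a remark on where immigrant communities live, and its reason is that all zones are covered. As a statement about who is invited, that is correct. The next sentences expect different levels of sensitisation to appear in the results, and the preceding paragraph already names poor collaboration as the main limitation. This shows that participation was not overlooked. It does not rescue the conclusion: even on the narrow reading, zones would be represented in proportion to their staff only if response were equal across centres, and the article expects it to differ.

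Several further points stand and limit the concern:

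- Stratification is not the only measure. Researchers will visit centres, hold a dedicated session in each, and have a local person collect forms from absentees within two weeks.
- The article says without condition that differing participation will be taken into account. Only the stratification is conditional, and its natural trigger is the participation rates, not the answers.
- Professional category is not ignored: the Analysis plan examines the items by category and by centre. What is lacking is an overall percentage standardised for unequal response.
- Weighting to headcounts cannot reach self-selection within a centre or category, as case (a) shows.

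A reader might go further and infer that the results will look too favourable and that training needs will be understated. The article does not support that. Nothing in it shows that exposed or interested staff respond more often. The previous survey's result that "17% were not interested in the subject" was obtained among people who were surveyed, so uninterested staff did respond. That survey's detection figures (21%, 7% and 5% across professional groups) show that contact with cases varies by category, but not that response does.

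**Conclusion.** The assurance that exposure cannot bias the results is unsupported and conflicts with the article's own expectations of voluntary participation, about 75% response and differing participation by centre. The possible bias is 2.5 points per 10-point gap between responders and non-responders; an observed 44% is compatible with 33% to 58% at the extremes. These figures rest on the 75% being realised. The gap and its direction are unknown, and the differential response and knowledge values in the worked cases are assumptions. Stratifying by participation rate when judged necessary does not correct an overall percentage. Weighting to headcounts corrects the between-centre and between-category part; what remains has to be stated and bounded.

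**What to change.** 1. In the Discussion, replace the claim of no exposure-based bias with a statement that non-response by professionals is a limitation whose direction is not known in advance.
2. For the percentages under objectives 1 to 3 and 5, always report, beside the unweighted figures, estimates weighted to aggregate staff headcounts by team and, where available, professional category. Remove the condition on the participation adjustment.
3. Compare responders with those headcounts by team and category.
4. State that weighting does not remove self-selection within a centre or category. For the main knowledge items, show a simple sensitivity range using the formula in step 2 of the working, with the non-responder rate varied in both directions.

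The cost is modest. Team codes and per-centre response rates are already planned and professional category is already collected, so the new material is aggregate headcounts by category and one further analysis. Aggregate counts identify no individual, which keeps the promised anonymity. The stated uncertainty becomes slightly wider.

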## Abbreviations

**EU**: European Union; **FGM**: Female Genital Mutilation; **PHC**: Primary Healthcare Centre; **UN**: United Nations Organization; **UNFPA**: United Nations Population Found; **UNICEF**: United Nations Children's Found; **WHO**: World Health Organization.
